## Abstract

**Introduction:**

Pelvic floor muscle training (PFMT) exercises and neuromuscular electrical stimulation (NMES) are described as conservative interventions to prevent or treat female stress urinary incontinence (SUI). However, it has not been described yet the effect of PFMT associated to intravaginal NMES which evaluated the cost-effectiveness and cost-utility of treating.

**Aims:**

To evaluate the effects of intravaginal NMES associated with the PFMT protocol on urinary loss and quality of life in women with SUI and to evaluate the cost-effectiveness and cost-utility and pelvic floor muscle in women with SUI.

**Methods:**

Randomized controlled trial study with economic evaluation. Inclusion criteria are woman (biological), aged ≥ 18 years old and with a report of SUI ≥ once/week. Exclusion criteria are presence of vaginal or urinary infection, virginity, being in the gestational or puerperium period, or neurological disease. Participants will undergo physical therapy assessment and intervention: anamnesis, pelvic floor muscle assessment by vaginal palpation and manometry (Peritron^TM^), questionnaires (Short-Form 6 Dimensions—Brazil (SF-6D), King's Health Questionnaire (KHQ) and King´s Health Questionnaire for Scoring Algorithm), health costs, and voiding diary. Participants will be randomly allocated into 3 groups: CG (control group), IG 1 (intervention group 1, PFMT), and IG2 (intervention group 2, PFMT + NMES). The statistical analysis will be performed by intention to treat, and multivariate analysis of mixed effects will be used to compare outcomes. Effect size measurements will be calculated and will be provided by Cohen’s *d* test. A significance level of 5% will be adopted. Additionally, the incremental cost-effectiveness and incremental cost-utility ratios will be used.

**Discussion:**

This protocol can corroborate with the literature in order to identify the effect of techniques, based on the possibility of confirming the hypothesis that the NMES associated with PFMT performed concurrently will be the best treatment option; considering the effectiveness, cost-effectiveness, and cost-utility analysis, it will be used as an option for optimization of the treatment of SUI.

**Trial registration:**

Brazilian Registry of Clinical Trials (ReBEC) ID: RBR-6gtzg4. Registered on September 3, 2019.

## Introduction

The International Continence Society defines urinary incontinence (UI) as any involuntary loss of urine [1]. UI is defined as stress urinary incontinence (SUI) when the loss of urine is associated to an effort or a physical exertion, cough, or sneeze. The prevalence of SUI between women range from 3 to 25%, and elderly women seem to be the most affected by SUI [2]. Changes in habits, physical inactivity, and social isolation may be associated to SUI, since women may feel embarrassed due to episodes of loss of urine during some activities [3–5]. In addition, the prevalence of SUI may have an important economic impact, since the use of hygienic protectors and routine care or consultations, as well as surgical interventions for the treatment of SUI, is associated with high costs [6].

Pelvic floor muscle training (PFMT) is considered the first-line of prevention and treatment of SUI, with level 1 of evidence and recommendation A [7–9]. Besides PFMT, neuromuscular electrical stimulation (NMES) is considered another available resource to be applied during the SUI treatment and is indicated as a second line of treatment when its use is combined with PFMT [10]. NMES is used as an attempt to recover urinary continence mechanisms by strength gain of pelvic floor muscles (PFM) [11], once the stimulation of the efferent motor fibers of the pudendal nerve causes a direct contraction of PFM or the striated periurethral musculature, enabling the mechanism of closure of the urethral sphincter [12].

However, a systematic review [10] identified that the effect of NMES associated with other therapeutic methods (drugs, PFMT, and vaginal cones) are inconclusive. Although the application of NMES versus PFMT indicated a cure and improvement of SUI reported by women and improved PFM function in the group that underwent treatment with PFMT compared to NMES, no differences were found in the outcomes related to quality of life and quantification of urinary symptoms. In addition, data related to treatment satisfaction, measures of quality of life of general health status, and economic data were not reported.

Data related to the economic analysis in health costs may be considered a relevant tool to be evaluated during SUI treatment. Studies that aim to identify the cost-effectiveness and cost-utility of a specific intervention may be used by governments’ institutions during the decision-making regarding the best evidence-based intervention that may correct the public health problems according their direct finite resources [13]. In Brazil, there are no estimates regarding annual expenses for the treatment of UI. However, it is known that more than $16 billion are spent on UI treatment in the USA annually [14]. It is expected that the economic analysis may affect directly the development of new guidelines related to the clinical practice of health professionals who treat women with SUI.

Therefore, the primary aim of this study is to evaluate the effects of intravaginal NMES associated with the PFMT protocol on urinary loss and quality of life in women with SUI. The secondary aim is to evaluate the cost-effectiveness and cost-utility and pelvic floor muscle in women with SUI.

The hypothesis of the study is that both treatments (NMES associated with PFMT and PFMT) will present good effectiveness; however, considering greater cost-effectiveness, PFMT will be the best option.

## Methods

### Trial design

This is study is a randomized controlled trial with a blind assessor and economic evaluation. Outcome measures will be assessed at baseline (before treatment begins), on the last day of treatment (after the 10th session), and up to 6 months after the treatment is completed (follow-up). From January 2022, participants will be invited and randomized into three groups by a simple randomization using an electronic system “Randomization Main” and a ratio of 1:1:1. The data for the primary outcome will be collected until the end of 2023 and the follow-up data until the first semester of 2024. This project will follow the guidelines of the *Consolidated Standards of Reporting Trials* (CONSORT) and *Standard Protocol items: recommendations for interventional trials* (SPIRIT) [15] items.

### Ethics

The present research was approved by the Ethics and Research Committee of the Federal University of São Carlos. Before the data collection, each participant will receive clarifications about the research objectives, the anonymity of their data, and the freedom to participate and will sign two copies of the informed consent form. This study was registered in the Brazilian Registry of Clinical Trials (ReBEC) under the number http://www.ensaiosclinicos.gov.br/ ID: RBR-6gtzg4, date of registration: September 03, 2019.

After the inclusion of the participant in the study, the subjects will receive a numeric code in order to keep the personal information unidentifiable. In addition, information regarding the telephone number, cell phone, and home address will be kept under the care of the researcher responsible for the project and will not be disclosed in scientific events or papers.

In any case of change, participants will be communicated by the responsible researcher after changes were performed at the Brazilian Registry of Clinical Trials (*Registro Brasileiro de Ensaios Clínicos*—REBEC).

### Participants and settings

The clinical trial will be conducted at the Women’s Health Research Laboratory, Physical Therapy Department, Federal University of São Carlos, Brazil. Participants will be invited through an informal invitation on social media sites (e.g., Facebook and Instagram), leaflets, newspapers, websites, and radios. After selecting the participants, a subjective interview will be conducted in order to assess the sample eligibility.

This study will include women (biological), aged ≥ 18 years, with a report of SUI ≥ once a week [16], with SUI symptoms that will be determined by the affirmative answer to the following *King’s Health Questionnaire* (KHQ) question [17]: “Did you involuntarily lose urine associated with coughing, sneezing, exercise or weight lifting in the last month?” Participants will be excluded if they present vaginal or urinary infection, if they were virgins, and if they were pregnant or in the puerperium period for at least 1 year, are women with neurological disease, and are participants with the incapacity to perform a PFM contraction.

### Measurement of results, primary and secondary outcomes

Outcome measures will be evaluated in several stages: at the beginning (before the beginning of interventions) and at the end of 10 sessions (subjective interview, pelvic floor muscle assessment, KHQ, Short-Form 6 Dimensions- Brazil, King´s Health Questionnaire for Scoring Algorithm and voiding diary). During the follow-up, the outcomes measures will be evaluated by telephone for 6 months. The economic evaluation will be performed during the 6 months of follow; however, at the 3rd and 6th follow-up assessment, we will apply the KHQ, Short-Form 6 Dimensions—Brazil, King’s Health Questionnaire for Scoring Algorithm, additional to the economic evaluation.

The primary outcomes will be urinary symptoms and impact of UI on quality of life. The secondary outcomes will be health cost analysis and PFM function. The impact of UI will be carried out using the KHQ and Short-Form 6 Dimensions—Brazil (SF-6D) questionnaires. Urinary symptoms will be assessed by the voiding diary that will be given to the participant. Cost analysis will be investigated by questionnaires and the PFM function will be assessed by vaginal palpation and manometry.

### Evaluation tools

The objectives of the study will be explained by the responsible researcher, who will clarify all doubts related to the research, and the participants who agree to participate will sign the informed consent form. After the informed consent form was signed, one physiotherapist responsible for the participants’ evaluation will carry out an subjective interview that will include questions related to the personal data, sociodemographic, urogynecology, and obstetric aspects, such as age, profession, years of study, marital status, presence of any disease, urinary complaints, hormone replacement therapy, gestational history, pelvic or abdominal surgery, current urinary tract infection, and previous UI treatment.

Subsequently, the PFM function assessment will be performed by vaginal palpation and manometry. The participant will be ask to position herself in supine position with her hips and knees flexed at 45° and feet supported [18]. To perform the evaluation, the examiner will wear disposable gloves and use lubricant gel. PFM function will be assessed by bidigital vaginal palpation, associating the PERFECT (Table 1) and using the graduation in accordance with the Modified Oxford Scale (MOS) (0 = absence of contraction; 1 = flicker; 2 = weak; 3 = moderate; 4 = good; 5 = strong) [18]. Intra-rater reliability of bidigital vaginal palpation performed by the examiner of the present study was already reported and was considered substantial (κw = 0.75) [19].

**Table 1 Tab1:** PERFECT scheme

**P**	“Power”: evaluation of a maximal voluntary contraction, graduated by MOS scale
**E**	“Endurance”: time (in seconds) that participant can sustain the contraction with the same degree obtained during the “P” item assessment, considering the maximal time of 10 s
**R**	“Repetitions”: repetition of the “E” item task, performing a 4-s rest between each repetition. The largest number of repetitions is 10
**F**	“Fast contractions”: assessment of the largest number of vigorous and quick contractions (“contracting and relaxing”) until fatigue performed by the participants, with the same strength degree graded in “P” item. Limited to 10 PFM contractions.
**ECT**	“Every Contraction Timed”: the time and sequence of events mentioned above will be timed and recorded

Participants will be instructed to perform the PFM contraction with the following verbal commands: (i) “Contract the pelvic floor muscles as if you are holding the urine”; (ii) “Make a movement with the muscles upwards and inwards”; (iii) “Inhale when your muscles are relaxed and exhale when your muscles are contracting”; and (iv) “Try not to contract the abdomen, glutes or leg muscles while contracting the pelvic floor muscles.” In addition, participants will be instructed to perform the highest contraction strength during three repetitions of maximal voluntary contractions, described by “P” item of PERFECT’s scheme. The highest degree of contraction force will be used in statistical analysis. An interval of 1 min will be adopted between repetitions. The assessor will direct verbal words of encouragement (“hold, hold, hold”) during the contraction.

Five minutes after vaginal palpation, manometry will be performed using the Peritron^TM^ manometer (Cardio Design Pty Ltd, Oakleigh, Victoria, Australia), graded from 0 to 300 cmH_2_O, with a vaginal probe (28 × 55 mm) attached. The manometry will be performed at the same positions and by applying the same verbal instruction as the vaginal palpation. Vaginal probe will be introduced in the participant’s vaginal canal (the tube will be coated with an un-lubricated condom and with a neutral lubricating gel). After calibrating the device, three maximal voluntary contractions of 5 s will be requested and recorded [20]. The validity [21] and intra-rater reliability of the Peritron manometer is already reported and considered good (ICC > 0.90) [22].

The related quality of life and urinary impact will be assessed by the KHQ questionnaire validated to Brazilian Portuguese [17]. This questionnaire consists of 30 questions that assess items related to health perception, impact of urinary incontinence, limitations of daily activities, physical and social limitations, personal relationship, emotions, and sleep/energy, in addition to measures of severity. The score of this questionnaire ranges from 0 to 100, and the higher the score, the worse the quality of life. A change in the baseline of at least 5 points (minimally clinically important difference) in the domains cited above indicates significant change and a clinical improvement in health-related quality of life after treatment [23].

To assess the presence of urinary symptoms, participants will be instructed to complete a 24-h voiding diary. This instrument contains questions related to the urinary habits, such as the information on number of urinations, amount of urine eliminated, and occurrence of urinary loss. In addition, the voiding diary will quantify the use of absorbents, diapers, and linings (if used and the number of changes) [24, 25]. Participants will be encouraged to complete the voiding urinary twice: once at the pre-treatment before the beginning of the intervention and at the end of the treatment (10th session). The results from the voiding diary will be analyzed by urine loss frequency, considering the urinary leakage associated to stress (e.g., coughing, sneezing, physical exercise or household activities).

Health costs related to UI will be assess by two different questionnaires: (i) SF-6D, validated to Brazilian Portuguese by Campolina et al. [26], and (ii) *King´s Health Questionnaire for Scoring Algorithm*, elaborated by Brazier et al. [27]. The SF-6D evaluates items related to functional capacity, global limitation, physical aspects, emotional aspects, social aspects, pain, mental health, and vitality. This questionnaire allows to generate utility indexes (adjusted by years of life) from data of effectiveness used in economic analyzes. The *King´s Health Questionnaire for Scoring Algorithm* is based on specific health measures of UI, which assesses utility based on quality of life with a five-dimensional classification: functional limitation, physical limitation, social limitation, emotions, and sleep. This questionnaire presents a score of validity pointed in 0.62. Both questionnaires have a unique score ranging from 0 to 1 (where 0 represents the worst health status and 1 represents the better health status) [27].

The psychometric properties of the instruments and procedures are present in Table 2.

**Table 2 Tab2:** Psychometric properties of the instruments and procedures

Examination procedure	Description of procedure	Indicator of musculoskeletal dysfunction	Reported psychometric properties
Modified Oxford Scale (MOS)	Vaginal palpation performed by introduce of two fingers inside participant vaginal canal	Subjective evaluation of PFM function	Intra-rater reliability of MOS (Kappa test) [19] Bidigital palpation 0.75 Inter-rater reliability of MOS (Kappa test) Bidigital palpation 0.60
Manometry	Peritron^TM^ manometer: insertion of a probe into the vaginal canal of participant	Objective evaluation of PFM function	Intra-rater reliability 0.96 [28]
KHQ	Score variating 0 to 100 = the higher the score, the worse the quality of life	Impact of urinary loss	Internal consistency 0.87 [17] Reproducibility: evaluated by Pearson’s coefficient for all domains [29] (listed below): Perception of health 0.36 Impact of incontinence 0.60 Limitations of daily activities 0.75 Physical limitation 0.74 Social limitation personal relationship 0.82 Emotions 0.76 Sleep/energy 0.62 Severity measures 0.71 Minimum relevant clinical difference: 5 points [23] Responsiveness: evaluated by Cronbach’s alpha for all domains [30] (listed below): General health perception − 0.76 Impact of incontinence − 1.94 Role limitations − 1.50 Physical limitations − 1.49 Social limitations − 1.33 Personal relationships − 0.76 Emotions − 1.44 Sleep/energy − 0.86 Severity measures − 2.40
SF-6D	Score between 0 to 100 = the higher the score, the better the health status	Quality of life that constructed data about effectiveness, used in economic analyzes	Internal consistency: – Reproducibility intra-rater: evaluated by Pearson’s correlation coefficient for all domains [31] (listed below): Functional capacity 0.8 Physical aspects 0.63 Social aspects 0.75 Emotional aspects 0.44 Pain 0.54 Vitality 0.65 Mental health 0.69 General health status 0.84 Specificity: – Minimum relevant clinical difference: – Responsiveness: 0.404 (performed in women with postoperative pelvic organ prolapse; the value of the total score was used to identify the result of responsiveness through the ANOVA test) [32]
King’s Health Questionnaire for Scoring Algorithm	Score: 0 = worst health status 1 = better health status	Health measures of UI	Internal consistency: – Reproducibility: – Specificity: – Minimizes relevant click difference: – Responsiveness: evaluated by standardized response mean (SRM) for all domains (listed below). The SRM is a version of the effect size that divides the mean change by the standard deviation of the change [27]: Role 0.56 Physical 0.51 Social 0.39 Personal 0.33 Emotions 0.37 Sleep 0.41 Severity 0.50 Valid: –

MOS, Modified Oxford Scale; PFM, pelvic floor muscle; KHQ, King’s Health Questionnaire; SF-6D, Short-Form 6 Dimensions—Brazil; UI, urinary incontinence

A semistructured questionnaire will be used to assess the economic data related to the health services use. In addition, the use of medications, history of medical consultation and/or emergency care, history of hospitalizations related to urinary problems, and surgical procedures will be verified and will be followed up for 6 months. The cost of which treatment for each participant will be assessed according to the use of health services and calculated by the price list of the Brazil’s Unified Health System and according to the physiotherapist’s fees established by the Federal Council of Physiotherapy and Occupational Therapy and also by average of three budgets for private treatment. Costs will be computed with the use of sanitary napkins, diapers and liners, medications, exams related to urinary problems, consultation with health professionals (such as nurses, doctors and/or physiotherapists), and other interventions and surgical procedures.

In order to compose the economic evaluation, the expenses related to materials used during physical evaluations and intervention (such as gloves, condoms, lubricants, disposable sheets, pressure gauge, NMES devices and probes, and the physiotherapist assessment price) will be computed. In addition, to compose the health costs of tertiary care, information related to hospitalization history, surgery history, average hospitalization time, and absenteeism for health reasons will be verified. To convert the procedures into current currency, the values informed by the Brazil’s Unified Health System price tables and/or based on the market average price will be used. Monetary data will be made in the national currency (real) and converted into international currency with an updated conversion rate.

To compose the indirect costs, the participants will be asked about the days of absence from work (paid or unpaid), which will be computed by means of specific price weights for the female gender and transportation to get to the place where the treatment will be carried out. In addition, the distance between the participants home to the location where the treatment will be applied will be computed. Therefore, the price of the means of transport for those using public transport or weighting of the price of the fuel of private transport will be assessed.

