At the interview and physical assessment, the subjective interview record will be applied, which generates qualitative variables that will be presented as frequencies and percentages and quantitative variables that will be presented as minimum value, maximum value, mean, median, and standard deviation. One researcher will perform the vaginal palpation and the manometry assessment, as well as applied SF6-D, KHQ, King´s Health Questionnaire for Scoring Algorithm, health cost analysis form, and 24 h-voiding diary, which will result in quantitative scales that will be presented as minimum value, maximum value, mean, median, and standard deviation.At the end of treatment sessions, vaginal palpation and manometry will be repeated, as well as SF6-D, KHQ, King’s Health Questionnaire for Scoring Algorithm, health cost analysis form, and the 24 h-voiding diary, which will result in quantitative scales that will be presented as minimum value, maximum value, mean, median, and standard deviation.At the 1st to the 6th month of follow-up, the health cost analysis form will be applied, and at the 3rd and 6th month of follow-up, the SF6-D, KHQ, King´s Health Questionnaire for Scoring Algorithm, and health cost analysis form will be completed, which will result in quantitative scales that will be presented as minimum value, maximum value, mean, median, and standard deviation.At the end of the treatment, the ANOVA for repeated measurements will be applied to verify the effects of the three groups and the two stages (pre-treatment and re-assessment after finished the intervention protocol) and the interactions between them according the results related to the vaginal palpation, manometry, SF6-D, KHQ, King´s Health Questionnaire for Scoring Algorithm, health cost analysis form, and 24 h-voiding diary, if the residues present normality. If the residues do not present normality, a non-parametric test will be applied.At the end of the follow-up, the repeated measures ANOVA will be applied to verify the effects of the three groups and the eight stages (pre-treatment, re-assessment after finished the intervention protocol and 1, 2, 3, 4, 5, and 6 months of the follow-up) and the interactions between them considering the SF6-D, KHQ, King’s Health Questionnaire for Scoring Algorithm, health cost analysis form, and 24 h-VD, if the residues present normality. If the residues do not present normality, a non-parametric test will be applied.The cost-utility assessment will be performed by the quality-adjusted life years (QALY), which combines the length and quality of life into a single index number between 0 and 1, where 0 corresponds to a health state judged to be equivalent to death and 1 corresponds to optimal health [35, 36]. To conduct the statistical analysis, the mean between-group cost differences will be corrected for their baseline, and the total costs will be divided by the costs differences for incremental analysis of cost-effectiveness and cost-utility ratios. Subsequently, a deterministic cost-utility value and a probabilistic one will be determined by applying a bootstrapping technique of 5000 interactions and the bias-corrected, in order to compare health costs between groups. The results will be presented with the confidence interval of 95% (95% CI). The likelihood of the cost-effective intervention will be estimated by the cost-effectiveness acceptability curves to compared values other than willingness to pay [37]. The Kaplan-Meier method and the Log-Rank between-group comparison test will be applied in order to assess the sensitivity of the uncertainty of each parameter by assessing the changes in the results in the range of parameter values [38].

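### Stress leaks, a primary outcome, are counted on one day before and one day after treatment although women qualify with one leak a week; a longer diary and a count model would measure them better

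*Protocol article*

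**What the plan says.** - **Outcome.** Measurement of results, primary and secondary outcomes: "The primary outcomes will be urinary symptoms and impact of UI on quality of life". The instrument for the first is fixed there too: "Urinary symptoms will be assessed by the voiding diary that will be given to the participant".
- **Window.** Evaluation tools: "participants will be instructed to complete a 24-h voiding diary". "Participants will be encouraged to complete the voiding urinary twice: once at the pre-treatment before the beginning of the intervention", and again at the 10th session. "The results from the voiding diary will be analyzed by urine loss frequency", restricted to leaks on effort.
- **Entry.** Participants and settings admits women "with a report of SUI ≥ once a week".
- **Analysis.** The Statistical analysis plan section tests group, stage and their interaction by repeated-measures ANOVA if the residuals pass Shapiro-Wilk. Otherwise: "If the residues do not present normality, a non-parametric test will be applied".
- **Timing elsewhere.** The same section compares urine loss over four stages, and its list of details puts the 24-h diary into an eight-stage ANOVA. That list leaves the diary out of the instruments completed at months 3 and 6.
- **Sample size.** It rests on KHQ points alone; no assumption is made for the diary.

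**The concern.** The entry criterion works on a scale of weeks and the outcome on a scale of one day. A woman at the threshold averages 1/7 = 0.14 leaks per diary day. She will usually record none at baseline and then cannot show a fall. For women who leak more often, one day is still a noisy sample of their usual frequency.

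The analysis rule adds to this. One-day counts are small integers with many zeros, so their residuals are poor candidates for a normality test. If the test fails, the ANOVA that would estimate the group-by-stage effect is set aside. At stake is whether a real reduction in leakage would be detected, and whether it could be reported in a unit that clinicians can use.

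**Working it through.** **Inputs from the protocol.** Diary window 1 day, completed twice; entry at 1 or more leaks a week; 44 women per group, of whom 4 allow for loss, leaving 44 − 4 = 40. There is no planned figure for the diary to reproduce.

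**Assumed inputs.** Weekly leak rate *r* (3, 7 and 14 shown, plus the threshold of 1), overdispersion *k* (0.5, 1, 2), and a halved rate in one arm. The protocol gives none of these.

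**1. Chance of a zero record.** Over *d* days the mean is μ = *r*·*d*/7. Poisson: P(0) = exp(−μ). Negative binomial with *k* = 1: P(0) = 1/(1 + μ).

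| Leaks/week | 24 h, Poisson | 24 h, *k* = 1 | 3 days, Poisson | 7 days, Poisson |
|---|---|---|---|---|
| 1 | 87% | 88% | 65% | 37% |
| 3 | 65% | 70% | 28% | 5% |
| 7 | 37% | 50% | 5% | 0.1% |
| 14 | 14% | 33% | 0.2% | <0.1% |

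Under Poisson, zeros are the majority of 24-h records below 7·ln 2 = 4.9 leaks a week.

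**2. Illustrative power.** Two arms of 40, post-treatment counts only, two-sided 5%, μ₂ = μ₁/2:

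var(log rate ratio) = (1/μ₁ + 1/μ₂ + 2*k*)/40; power = Φ(ln 2/SE − 1.96).

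Example, *r* = 3, 24 h, *k* = 1: μ₁ = 0.429, μ₂ = 0.214. The variance is (2.333 + 4.667 + 2)/40 = 0.225, so SE = 0.474. Then ln 2/SE = 1.461 and power = Φ(−0.499) = 31%. For 7 days: (0.333 + 0.667 + 2)/40 = 0.075, SE = 0.274, power = Φ(0.571) = 72%.

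| Leaks/week | *k* | 24 h | 7 days |
|---|---|---|---|
| 3 | 1 | 31% | 72% |
| 7 | 0.5 | 59% | 96% |
| 7 | 1 | 50% | 80% |
| 7 | 2 | 38% | 55% |
| 14 | 1 | 65% | 84% |

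A 3-day diary with *k* = 1 gives 56% at 3 a week and 72% at 7. Extra days shrink only the 1/μ terms. The 2*k* term reflects differences between women, which a baseline covariate can reduce.

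**3. A check nearer to the planned tests.** Simulation: two arms of 40, 1,000 runs per setting, each woman's weekly rate equal to 1 plus a gamma-distributed excess, unchanged in one arm and halved in the other. With two groups and two stages, a t-test on change scores is the group-by-stage test.

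| Mean leaks/week | Change score, 1 day | Change score, 7 days | Rank test on post counts, 1 day | Rank test on post counts, 7 days |
|---|---|---|---|---|
| 3 | 21% | 81% | 35% | 87% |
| 7 | 37% | 97% | 50% | 84% |

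**4. The normality rule.** In the same simulation, Shapiro-Wilk on the pre-post change residuals rejected in 100% of one-day trials at a mean of 1 a week, 99.8% at 3, 96.5% at 7 and 92.5% at 14. With 7-day diaries it still rejected in 60–89%. A longer diary therefore does not settle the choice of analysis by itself.

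**5. Timing.** Two diaries (Evaluation tools) cannot supply four stages or eight (Statistical analysis plan).

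**The case against.** Once a week is a minimum, not an expected rate. If the women recruited average 14 leaks a week, zeros are a minority (14–33%) and one-day power is 65%. A reader might infer that most diary records will be zero or that a true effect will be missed. Without a baseline rate the documents support neither. Overdispersion is also assumed, and with *k* = 2 even a 7-day diary reaches only 55% at 7 a week. All of this stands, and it is why ranges are shown. The direction does not change: 7 days did better than one in every setting tried.

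The power formula is for a two-arm, post-only count comparison, not the planned ANOVA. That also stands. The formula speaks to the length of the diary and is no verdict on the ANOVA rule. The simulated change-score test is closer to the plan and points the same way.

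A reader might also infer that the fallback cannot deliver the planned group effect, or that normality is certain to fail. Both go too far. The protocol does not say which non-parametric test it means. Factorial methods for repeated measures can test an interaction, and a test on change scores uses the baseline. Leaving the test unnamed is no fault in an article whose full plan is not shown. What survives is narrower: rejection is very probable, and the usual rank tests then give no group-by-stage effect in leaks per day.

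Finally, seven days is not obviously a light task, because the diary also covers urinations, volumes and pad changes.

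**Conclusion.** The point holds as a mismatch between a weekly entry criterion and a one-day measurement of a primary outcome, made worse by an analysis rule that one-day counts will very probably fail. Its size depends on the unknown leak rate and overdispersion. Under the assumptions shown, 24-h power for a halved rate runs from 31% to 65%, against 55% to 96% for 7 days. A halved rate between arms is itself an assumption, and all three groups are asked to exercise daily at home. KHQ remains as the other primary measure and is not affected. Nothing here supports changing the analysis of KHQ or SF-6D. This is an inexpensive improvement that should be made, not a defect that invalidates the trial.

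**What to change.** 1. Reconcile the diary schedule first: Evaluation tools has it completed twice, while the Statistical analysis plan section analyses urine loss over four stages and the diary over eight.
2. Keep the same self-completed diary for at least 3 days, preferably 7, at each diary stage.
3. Analyse stress leaks with a negative binomial model: group, baseline count as covariate and log diary days as offset. Report the rate ratio with its 95% CI. Use this in place of the Shapiro-Wilk switch for this outcome only.

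**Cost.** A few more diary days per woman, some missing days (the offset handles unequal numbers of completed days), and a change of analysis wording. No new instrument or visit is needed. If the burden of 7 days is too great, 3 days gives part of the gain. If the diary must stay at 24 h, the count model can still be adopted and yields an interpretable effect, but it does not remove the floor: the count-based power at 3 leaks a week is still only 31%.
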